# Evaluating early administration of the hydroxymethylglutaryl-CoA reductase inhibitor simvastatin in the prevention and treatment of delirium in critically ill ventilated patients (MoDUS trial): study protocol for a randomized controlled trial

**DOI:** 10.1186/s13063-015-0731-0

**Published:** 2015-05-16

**Keywords:** Delirium prevention, Cognitive impairment, Statins, Beta-amyloid

## Abstract

**Background:**

The incidence of delirium in ventilated patients is estimated at up to 82%, and it is associated with longer intensive care and hospital stays, and long-term cognitive impairment and mortality. The pathophysiology of delirium has been linked with inflammation and neuronal apoptosis. Simvastatin has pleiotropic properties; it penetrates the brain and, as well as reducing cholesterol, reduces inflammation when used at clinically relevant doses over the short term. This is a single centre randomised, controlled trial which aims to test the hypothesis that treatment with simvastatin will modify delirium incidence and outcomes.

**Methods/Design:**

The ongoing study will include 142 adults admitted to the Watford General Hospital Intensive Care Unit who require mechanical ventilation in the first 72 hours of admission. The primary outcome is the number of delirium- and coma-free days in the first 14 days. Secondary outcomes include incidence of delirium, delirium- and coma-free days in the first 28 days, days in delirium and in coma at 14 and 28 days, number of ventilator-free days at 28 days, length of critical care and hospital stay, mortality, cognitive decline and healthcare resource use. Informed consent will be taken from patient’s consultee before randomisation to receive either simvastatin (80 mg) or placebo once daily. Daily data will be recorded until day 28 after randomisation or until discharge from the ICU if sooner. Surviving patients will be followed up on at six months from discharge. Plasma and urine samples will be taken to investigate the biological effect of simvastatin on systemic markers of inflammation, as related to the number of delirium- and coma-free days, and the potential of cholinesterase activity and beta-amyloid as predictors of the risk of delirium and long-term cognitive impairment.

**Discussion:**

This trial will test the efficacy of simvastatin on reducing delirium in the critically ill. If patients receiving the statin show a reduced number of days in delirium compared with the placebo group, the inflammatory theory implicated in the pathogenesis of delirium will be strengthened.

**Trial registration:**

The trial was registered with the International Standard Randomised Controlled Trial Registry (ISRCTN89079989) on 26 March 2013.

## Background

Delirium in critically ill patients is a manifestation of acute brain dysfunction. The incidence of delirium in mechanically ventilated patients, assessed using the Confusion Assessment Method for the Intensive Care Unit (CAM-ICU), is estimated at up to 82% [1]. Delirium and dementia are typically presented as separate entities, distinguished by the timing and duration of symptoms, but increasingly are thought to share common pathological mechanisms [2,3], Although the mechanisms by which delirium may predispose patients to long-term cognitive impairment after critical illness have not yet been elucidated, delirium is associated with inflammation and neuronal apoptosis, which may lead to brain atrophy [4]. A longer duration of delirium has been shown to be associated with worse global cognition at three and 12 months after ICU discharge, and with significantly higher ICU and hospital costs [5,6]. An intervention which reduces delirium could potentially translate to a reduction of long-term cognitive impairment and dementia [7].

There is little evidence that commonly used pharmacologic approaches to prevent or treat delirium during critical illness are effective [8,9]. Statins, in addition to decreasing cholesterol synthesis, have complex pleiotropic effects and have been hypothesised to both prevent and treat delirium via effects that may modulate the molecular pathways of inflammation and microglial activation [10].

An *in vitro* study comparing different statins for prevention of neurodegenerative conditions concluded that monacolin J derivatives (natural and semi-synthetic statins), which includes simvastatin, are the best candidates. This is due to their better lipophilicity and capacity to penetrate the blood–brain barrier, cholesterol-lowering effect on neurons with a satisfactory safety profile and *in vitro* protection against neuronal cell death caused by okadaic acid [11]. The aim of the Modifying Delirium Using Simvastatin (MoDUS) trial is to test the hypothesis that treatment with enteral or oral simvastatin (80 mg) will increase the number of delirium- and coma-free days in ventilated ICU patients up to 14 days. The effects of simvastatin treatment on biological mechanisms important in the development of delirium will also be explored, including inflammation biomarkers, anticholinergic activity and beta-amyloid (β-amyloid) [12,13].

### Methods/Design

West Hertfordshire Hospitals National Health Service (NHS) Trust is the Sponsor for the MoDUS trial. The trial will be conducted in accordance with the ethical principles that have their origin in the Declaration of Helsinki. The protocol is approved by the Newcastle and North Tyneside 1 Research Ethics Committee (REC reference: 12/NE/0383, 6 December 2012) and by the Hertfordshire Hospitals Research and Development consortium at Watford General Hospital. The trial is registered on the International Standard Randomised Controlled Trial Registry (ISRCTN89079989, assigned on 26 March 2013). It is funded by the Research for Patients Benefit programme, which is funded and managed by the National Institute for Health Research (NIHR). The trial is being coordinated by West Hertfordshire Hospitals NHS Trust, in partnership with Northern Ireland Clinical Trials Unit (NICTU). The trial will comply with the principles of Good Clinical Practice (GCP) and will be carried out in accordance with applicable legislation and the Standard Operating Procedures of West Hertfordshire Hospitals NHS Trust and the NICTU. The trial will be reported in line with the Consolidated Standards of Reporting Trials (CONSORT) 2010 guidelines [14].

The MoDUS trial is a single centre, randomised, double-blind, placebo-controlled, superiority phase II trial including adults admitted to the Watford General Hospital ICU who require mechanical ventilation in the first 72 hours of admission. The study has three distinct objectives: to investigate the efficacy of early statins administration during an ICU stay for the prevention of ICU delirium; to determine any improvement in related neurocognitive sequelae coupled with standard clinical outcomes; and to study the biological effect of simvastatin on systemic markers of inflammation as related to the number of delirium- and coma-free days, and the potential of cholinesterase activity and β-amyloid as predictors of the risk of delirium and long-term cognitive impairment [12,13].

### Eligibility criteria

Patients will be eligible for the trial if they fulfil the following criterion: adult patients in intensive care requiring intubation within the first 72 hours of admission. Patients fulfilling any of the criteria below will be excluded from the trial:Aged less than 18-years-old;Patient known to be pregnant or breastfeeding;Known allergy to statin drugs;Creatine kinase (CK) level more than 10 times upper limit of normal range within 72 hours of randomisation;Alanine transaminase (ALT) level more than eight times the upper limit of normal range within 72 hours of randomisation;Patients currently receiving ongoing and sustained treatment with any of the following; itraconazole, ketoconazole, HIV protease inhibitors, nefazodone, cyclosporine, amiodarone, verapamil, diltiazem, gemfibrozil or danazol;Uncomplicated elective surgery (planned admission, surgical procedure and recovery as predicted);Patient expected to be discharged within 48 hours of admission;Patients with severe renal impairment (estimated creatinine clearance less than 30 ml/minute) not receiving renal replacement therapy;Severe liver disease (Childs-Pugh score >12);Current or recent treatment (within two weeks) with statins, as statins will be continued assuming there are no contraindications according to normal unit practice;Physician decision that a statin is required for proven indication;Contraindication to enteral drug administration, such as patients with mechanical bowel obstruction (patients with high gastric aspirates due to an ileus are not excluded);Known participation in investigational medicinal product trials within previous 30 days;Consent declined;Treatment withdrawal likely within 48 hours;Non-English speaking patients or those who do not adequately understand verbal or written information orHistory of porphyria.

### Clinical outcome measures

The primary outcome of the MoDUS trial will be the number of delirium- and coma-free days in the first 14 days after randomization, during which the patient is alive and free from delirium and coma, and where days are counted as calendar days (from 00:00 to 23:59). The coma state in an ICU patient is determined by nurses using the Richmond Agitation and Sedation Score (RASS) and delirium is screened for using the CAM-ICU [15,16]. Patients are defined as delirious if they are awake enough to at least respond to verbal stimulation with eye opening and eye contact for less than 10 seconds (RASS score of −2) and screen positive for delirium. CAM-ICU needs to be negative at all assessments throughout a whole study day for the patient to be considered free from delirium.

There are a number of secondary outcomes in this trial, including: clinical outcomes, biological mechanisms, safety measures and outcomes related to the health economic evaluation. The clinical outcomes are incidence of delirium, delirium- and coma-free days in the first 28 days, delirium at 14 and 28 days, and days in coma at 14 and 28 days. For this investigation, a RASS score of −3, (movement or eye opening in response to voice but no eye contact) regardless of whether disease or sedative induced, is handled as part of the spectrum of coma. While the validation studies for the CAM-ICU have demonstrated that delirium can be diagnosed in patients with a RASS score of −3 at Watford, along with some other centres, we routinely classify a patient with such as score as unable to be assessed (usually due to sedation). We decided this because of the clinical relevance of a RASS score of −3 as shown by the Sedation Practice in Intensive Care Evaluation (SPICE) Study Investigators and ANZICS Clinical Trials Group who have demonstrated that early deep sedation, defined as RASS score −3 to −5, predicts delayed extubation and increased mortality [17].

Other secondary outcomes are the number of ventilator-free days at 28 days, mortality at six months, organ failure-free days, cognitive decline and healthcare resource use. Cognitive impairment at six months is assessed using the telephone interview of cognitive status, called Brief Test of Adult Cognition by Telephone (BTACT), which is a battery of cognitive tests validated for telephone use assessing immediate and delayed memory recall, working memory span, verbal fluency, inductive reasoning and speed of processing [18]. Cognitive decline will be estimated by taking into account the patient’s baseline cognitive function before admission to the ICU, as assessed using the Informant Questionnaire on Cognitive Decline in the Elderly (IQCODE), scored at recruitment and six months later [19].

### Biological mechanisms

A translational study of biological markers of inflammation, cholinergic activity and neurodegeneration to provide insight into the pathophysiology of delirium and the potential of β-amyloid as a predictor of the risk of lon- term cognitive impairment will be undertaken. Blood and urine are taken at baseline prior to study drug administration (day one), and on day three, seven, 14 and 28 (within 6 hours of study drug adminstration) while the patients continue to receive the study drug. Plasma inflammatory response biomarkers, which will include serum C-reactive protein (CRP, cytokines (including tumour necrosis factor alpha(TNF-α, interleukin (IL)-1, IL-6 and IL-8), proteases and anti-proteases, adhesion molecule expression, and coagulation factors will be analysed. In addition simvastatin plasma levels will be analysed.

Plasma β-amyloid measurement has emerged as a promising biomarker to identify elderly persons at risk of developing dementia [20]. Lower β-amyloid 42 and 42/40 levels have been associated with increased risk of developing Alzheimer’s disease. A study suggests that older adults without dementia and with lower β-amyloid 42/40 levels have an increased rate of cognitive decline over nine years compared with those with higher levels [21]. It may be that plasma β-amyloid 42/40 levels may be a predictor of those patients who are most at risk of developing cognitive impairment following ICU delirium, therefore serial β-amyloid 42 and 42/40 ratio levels will be measured. Delirium is associated not only with an unbalanced inflammatory response, but also with a dysfunctional interaction between the cholinergic and immune systems. In order to increase the understanding of the relationship between the cholinergic and immune systems with regard to delirium pathophysiology, we will also measure biomarkers plasma acetylcholinesterase and butyrylcholinesterase, as indicators of cholinergic function [22].

### Safety

Plasma will be collected from each patient on days three, seven, 14, 21 and 28 while the patient is on the ICU, for the purposes of safety monitoring. CK and ALT levels will be measured. The frequency of the following events will be reported: CK level over 10 times the upper limit of normal; ALT level over eight times the upper limit of normal; patients whose CK is elevated more than 10-fold who then require renal replacement therapy; serious adverse events (SAEs) and occurrence of suspected unexpected serious adverse reactions (SUSARs). If the patient needs an acute administration of amiodarone (manufacturer: Ibigen, Aprilia, Italy), the regime of the study drug will be changed: the patient will receive one tablet every other day.

### Health economic evaluation

Health-related quality of life will be measured using the EuroQol 5-dimension 5-level (EQ-5D-5 L) questionnaire [23] at the point of consent to continue and at six months post-randomisation, to calculate quality-adjusted life years (QALY) at six months. Data on the health and social care services used by all patients will be collected for the six-month post-randomisation period. Length of ICU stay (level three care), length of high dependency unit stay (level two care) and length of hospital stay will be recorded in the case report form (CRF), and patients will use logs to record post-hospital discharge health service use. They will be asked to refer to this when completing a questionnaire at six months. If questionnaires are not returned, non-responders will be contacted by telephone and a second questionnaire will be sent out if required. The cost-effectiveness of the treatment compared to the placebo will be assessed.

### Power and sample size estimate

The sample size calculation for this study has been initially based on data from the Awakening and Breathing Controlled trial published in 2008, using the mean delirium- and coma-free days of 10 at 28 days among patients without the study intervention [24]. Our pilot data showed a standard deviation of 4.14 in delirium and coma free days at day 14 in a similar cohort ([name], personal communication, September 2012) Assuming this standard deviation, and assuming a type I error of 0.05 and 80% power, a sample size of 64 patients per group is adequately powered to detect a difference of approximately 2 DCFDs between the intervention and control groups, or approximately 0.5 SD. Allowing for an estimated 10% loss to follow-up, the sample size required is 142. nQuery AdvisoR version 4.0 was used for the sample size analysis (Elashoff, JD 2000).

A flow chart for the protocol is outlined in Figure 1.

**Figure 1 Fig1:**
[figure not shown]
Flow diagram (following CONSORT 2010 Statement Guidelines).

### Trial conduct

The study will be conducted in accordance with the ethical principles that have their origin in the Declaration of Helsinki. Critically ill patients requiring mechanical ventilation within 72 hours of admission to intensive care will be assessed for eligibility. A screening log will be retained and anonymized. Written informed consent or assent will be gained for patients fulfilling inclusion criteria before beginning any research activities, which include taking baseline bloods. Consent will be sought from the patients themselves if this is possible, but it is recognised that in the majority of cases ICU patients will be unable to give informed consent due to delirium itself, or alterations in their level of consciousness caused by illness and therapeutic sedation. In this situation, consent will be sought from a personal legal representative (PerLR), who may be a relative, partner or close friend, or a professional legal representative (ProfLR), such as a doctor who is not connected with the conduct of the trial. The consent from the representative will remain valid until a decision on consent to continue is obtained from the patient. All surviving patients that regain capacity will be informed about the trial at the earliest opportunity, and asked for consent to continue the study. Patients may withdraw from the trial or be withdrawn by their PerLR or ProfLR at any time, without prejudice. Data recorded up to the point of withdrawal will be included in the trial analysis. The IQCODE for each patient will be completed by the PerLR, any close family members or a friend at the time of consent and recruitment. The patient registration form will be completed and submitted to the NICTU to confirm registration of the patient to the trial, in accordance with the study drug randomisation schedule, and the unique trial identifying number will be assigned at the time of recruitment.

Patient drug packs will be prepared by Victoria Pharmaceuticals (Belfast, UK), and distributed to the site. The 142 consecutive packs will contain either simvastatin or placebo according to a prearranged order dictated by the 1:1 variable block randomisation schedule decided by the use of a random number generator. Simvastatin (40 mg tablets) or identical placebo tablets will be packaged in a white opaque high-density polyethylene plastic container, which will be sealed with a tamper-evident seal and labelled in compliance with applicable regulatory requirements. The placebo and active tablets will be indistinguishable when crushed and dispersed in water for nasogastric tube administration. Each container will contain 70 tablets of the study drug for the treatment of one patient for 28 days (plus seven days coverage). Each pack will be numbered with the patient’s trial identifier. Treatment allocation will be blinded as all trial drugs will be packaged identically and identified only by a unique trial identifier. Recruited patients will be randomised to receive once daily simvastatin (80 mg, as two 40 mg tablets) or two identical placebo tablets administered enterally via a feeding tube or orally for up to 28 days.

Although the primary outcome is determined at 14 days, the study drug will be administered for up to 28 days in order explore if longer treatment is associated with sustained and greater effect; however, the 28 day measurement will be less reliable given an expected median ICU length of stay of nine days. The recruiting clinician will complete a trial prescription form detailing the unique trial identifier assigned to the patient at the time of randomisation, which also corresponds to the study drug pack to be prescribed. The first dose of the study drug will be administered as soon as possible, ideally within four hours of randomisation and after baseline samples are collected, and subsequent doses will be given at 12:00 am on the following calendar day. If, for any reason, a dose is not administered at the intended time, it may be administered subsequently, but not more than 12 hours after the intended time of administration. Any missed doses will be recorded in the CRF to monitor treatment compliance.

Delirium assessment using CAM-ICU will be performed twice by the bedside nurse per nursing shift, with a minimum of four hours between assessments. CAM-ICU is a routine assessment in all ICU patients, and nurses undergo regular updates and have regular access to advice from the ICU delirium study team. Blood and urine samples will be taken at baseline prior to study drug administration (day one) and on day three, seven, 14 and 28 (within 6 hours of study drug adminstration), while patients will continue to receive the study drug for analysis of inflammatory cytokines, β-amyloid and cholinesterase activity. The study drug will be discontinued if any one of the following conditions is met, prior to the maximum treatment period (28 days from randomisation):Study drug-related adverse event, defined as:CK level over 10 times the upper limit of normal;ALT level over eight times the upper limit of normal.Development of a clinical condition requiring immediate treatment with a statin;Discharge from the critical care environment;Death;Discontinuation of active medical treatment;Patient or relative request that the study drug should be discontinued orDecision by the attending clinician that the study drug should be discontinued on safety grounds.

At consent to continue, surviving patients who consented to the follow-up protocol will be approached and EQ-5D-5 L will be completed face-to-face. They will receive a service use log to record their use of health and social care services from hospital discharge until six months post-randomisation. All survivors will be contacted at six months by phone for an assessment of cognitive function using the BTACT. Any deaths after discharge from hospital will be identified using the NHS Patient Centre Database, in order to avoid contacting relatives of patients who have died. Trial patients will be asked to let the Chief Investigator (CI) know if they move house at any time after hospital discharge; the NHS Patient Centre Database will enable us to locate any who move without informing the CI. Patients will be posted a follow-up package at six months post-randomisation, which will include the IQCODE, the EQ-5D-5 L and the use of health and social care services questionnaire.

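### The printed time for the second dose, read literally, allows it within hours of the first; the clock time is ambiguous and the intended spacing is not stated

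*Protocol article*

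**What the plan says.** All of the dosing text is in Trial conduct.

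- Frequency: "Recruited patients will be randomised to receive once daily simvastatin (80 mg, as two 40 mg tablets) or two identical placebo tablets", for up to 28 days.
- First dose: "The first dose of the study drug will be administered as soon as possible, ideally within four hours of randomisation", once baseline samples have been taken. No clock time is attached.
- Later doses: "subsequent doses will be given at 12:00 am on the following calendar day".
- Late doses: a dose not given when due may be given up to 12 hours after its intended time. This is the only other timing limit. No minimum interval between doses appears.

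Clinical outcome measures defines a study day for the primary outcome, "where days are counted as calendar days (from 00:00 to 23:59".

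On where dosing and monitoring end:

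- Trial conduct lists, among the events that stop study drug, "Discharge from the critical care environment". The term is not defined. The same list includes CK over 10 times and ALT over eight times the upper limit of normal.
- Safety says "Plasma will be collected from each patient on days three, seven, 14, 21 and 28 while the patient is on the ICU", and CK and ALT are measured on those samples.
- Health economic evaluation records the two kinds of stay separately: "Length of ICU stay (level three care), length of high dependency unit stay (level two care").
- The Abstract ends daily data at day 28 or at ICU discharge, whichever comes first.

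**The concern.** The first dose floats with the time of randomisation and the second is fixed to a clock time. If that clock time is the very start of the next calendar day, a patient first dosed in the evening is due a second full dose a few hours later. A once-daily schedule would ordinarily lead a reader to expect something near a day between doses, and nothing in the text guards against a short gap. The article does state a minimum spacing elsewhere, for delirium assessments.

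The stakes are exposure at the start of treatment and the accuracy of the exposure record. The article itself treats exposure as safety-relevant: it excludes patients on certain co-medications and changes the regimen when amiodarone is needed. The clock time also fixes when the biomarker samples fall, since they are tied to within six hours of dosing.

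The second, lesser issue is that the rule ending dosing and the rule ending scheduled CK/ALT sampling name different places. If those places differ, a patient could be on drug with no scheduled CK or ALT test, although both are stopping triggers.

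**Working it through.** **Figure stated in the article.** The pack holds 70 tablets for 28 days plus seven days' cover at two tablets a day: 2 × (28 + 7) = 70, which matches. Both readings of the clock time use one dose per calendar day, so the pack size does not tell them apart.

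**Gap between doses one and two.** Let *t* be the clock time of the first dose in hours. The article does not restrict *t*.

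- Literal reading, 12:00 am = 00:00 of the next day: gap = 24 − *t*.
- Noon reading, 12:00 of the next day: gap = 36 − *t*.

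| First dose | Gap if 00:00 | Gap if noon |
|---|---|---|
| 06:00 | 18 h | 30 h |
| 12:00 | 12 h | 24 h |
| 18:00 | 6 h | 18 h |
| 20:00 | 4 h | 16 h |
| 23:00 | 1 h | 13 h |
| 23:59 | 1 min | 12 h 1 min |

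On the literal reading the gap never exceeds 24 hours and has no floor. On the noon reading it runs from just over 12 to 36 hours.

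**How often a gap would be short.** The article gives no distribution of first-dose times, so each line below rests on an assumption.

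- First doses uniform over 24 hours. Literal reading: gap under 12 h when *t* > 12, so (24 − 12)/24 = 50%; gap under 6 h when *t* > 18, so (24 − 18)/24 = 25%. Noon reading: none under 12 h.
- First doses uniform from 09:00 to 21:00. Literal reading: gaps of 3 to 15 h, with (21 − 12)/(21 − 9) = 75% under 12 h. Noon reading: gaps of 15 to 27 h.
- Recruitment from 09:00 to 17:00 with the dose exactly four hours later, so *t* = 13 to 21. Literal reading: gaps of 11 down to 3 h.

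**Late-dose window.** A second dose due at 00:00 may be given as late as 12:00, which lengthens the first gap. This is permission for a dose that was missed, not a spacing rule. The same window also allows about 12 hours between later doses: due 00:00, given 12:00, next due 00:00.

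**Dosing and monitoring windows.** Time on drug without scheduled CK/ALT sampling = (discharge from critical care, or day 28 if sooner) − (discharge from ICU).

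- If critical care means the ICU alone, this is zero.
- If it includes the high dependency unit, it is the high dependency stay, capped at day 28.

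The article gives no high dependency length of stay, so the second case cannot be sized. There is some textual support for the wider meaning: the Abstract names critical care stay as an outcome where Health economic evaluation lists ICU and high dependency stays. Biomarker sampling, by contrast, is tied to the patient still receiving study drug, so the article links one set of samples to exposure and the safety set to location.

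**The case against.** A reader might infer that the schedule breaches its own once-daily rule. It does not. The second dose falls on the next calendar day, so each calendar day carries one dose, and the article sets no spacing rule for the clock time to contradict.

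The strongest objection is that 12:00 am may simply be a slip for noon. There is mild internal support: if samples are drawn after the dose, midnight dosing would put them between 00:00 and 06:00. On the noon reading no patient dosed on time receives two doses within 12 hours. This stands as a possibility, but it does not remove the point. The printed text says something else, the two readings lie 12 hours apart, and the article does not settle which was meant. Nor is this detail that a condensed article may leave to the full protocol, because the article prints an operative time.

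It is also fair to say that the frequencies rest on assumed recruitment and dosing hours, and that four hours is given as an ideal limit rather than the expected delay. The formula and the worked clock times do not depend on those assumptions; the percentages do.

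On monitoring, a reader might infer that patients are definitely dosed after CK/ALT checks end, or that the stopping rule can then no longer operate. The document supports neither. This is a single-centre trial on one ICU, the term used in the stopping list may mean that unit, and no text says study drug continues on a high dependency unit. The separate stays appear in a resource-use list that says nothing about dosing. Even on the wider reading, the CK and ALT triggers are not confined to scheduled samples, so a clinically ordered test could meet them, and the attending clinician may stop the drug on safety grounds. What would lapse is scheduled sampling only.

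**Conclusion.** The dose-timing point holds as a matter of spacing and ambiguity. Followed literally, the text allows a second full dose within hours of the first: 4 hours after a 20:00 dose, 1 hour after 23:00. Half of first gaps would be under 12 hours if first-dose times were uniform over the day, which is an assumption. If noon was intended, the range is just over 12 to 36 hours and the short gaps disappear. Because this is a printed instruction with a possible safety consequence, it should be corrected.

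The monitoring point is secondary and conditional. It is a mismatch of terms that becomes a gap in scheduled CK/ALT sampling only if critical care includes the high dependency unit, and its size cannot be derived from the article.

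Neither point affects the sample size, power or type I error. The timing rule is the same in both arms, so it is no reason in itself to expect bias in the comparison.

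**What to change.** 1. In Trial conduct, reconcile the clock time for later doses with the once-daily spacing the sponsor intends. Print the time in 24-hour notation and state the intended interval between doses one and two. Check that the drug chart and CRF instructions say the same.
2. Reconcile Safety with the discontinuation list in Trial conduct so that dosing and scheduled CK/ALT sampling end at the same named event, and define the critical care term. Check that the end of daily data collection in the Abstract is consistent with it.

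Which timing or stopping rule is right is for the clinical team; this review proposes none.

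The cost is a clarifying amendment and a check of the drug chart and CRF. Trial status reports 99 patients recruited as of March 2015, so 142 − 99 = 43 remained to be enrolled and could benefit. For patients already enrolled, the recorded dose times, if the CRF holds them, would show which reading was followed.
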